### Enrolment and randomisation

Those patients who satisfy the screening criteria and agree to study participation are enrolled and randomised at 1:1 to one of the two treatment arms. A web-based randomisation system (sealed envelope) performing stratified blocked randomisation will be used stratifying by baseline mJOA (<12 vs ≥12), age (<60 years vs ≥60 years) and time to onset of the disease (>6 months vs ≤6 months); random block size will be used. Throughout randomisation and follow-up, the subjects, physicians and data collectors remain blinded to group allocation.

### Treatment description and dosage modification

The investigational medicinal product (IMP) is a 24–34-week course of Ibudilast or matched placebo in an escalating dosage regimen up to a maximum of 100 mg daily if tolerated. The escalating dosage regimen is to minimise gastrointestinal side effects. Ibudilast is available in 10 mg capsules, and therefore the IMP will be provided as such. The placebo is identical in shape, size and colour to the Ibudilast capsule, and participants will be provided with the same instructions.

Participants will start treatment within 10 weeks prior to surgical decompression and will continue taking drug for up to 24 weeks postsurgery. The excretion half-life of Ibudilast is approximately 20 hours. The IMP will be taken in divided doses, twice daily, morning and evening, for a maximum of 34 weeks. Because this is the first surgical trial with Ibudilast, and to mitigate any potential interference on the coagulation system, treatment will be halted 5 days prior to surgery and resumed at the previous maximum dose right after operation.

Ibudilast is associated with gastrointestinal side effects, such as nausea and dyspepsia. Alongside dose escalation, participants will be instructed to take trial medication with food or within an hour of eating to improve gastrointestinal tolerability. In the event of minor gastrointestinal complaints, participants will be offered symptomatic treatment in the first instance, in conjugation with ongoing IMP therapy. If this is unsuccessful, or not agreeable to participants, the trial therapy will be decreased in decrements of 20 mg every 5 days, until a tolerable dosing level is achieved, or the drug is stopped. If a participant cannot tolerate a minimum daily dosage of 60 mg despite additional supportive measures, treatment within the trial will be stopped.

### Surgery

There are a number of different approaches used to decompress the spinal cord in DCM. No surgical approach has been shown to be superior, and the consensus is that the approach needs to be tailored to the specific anatomy. The surgical care of participants will therefore be at the discretion of the treating clinician and not protocolised.

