## Methods

### Study design and objectives

RECEDE-Myelopathy is a multicentre, double-blind, randomised, placebo-controlled trial assessing the efficacy of Ibudilast as an adjuvant treatment to decompressive surgery for DCM. Participants will be randomised to receive either 60–100 mg Ibudilast (interventional arm) or placebo (control arm) starting within 10 weeks prior to surgery and continuing for 24 weeks after surgery for a maximum of 34 weeks of treatment. Preoperative treatment may leverage the effects of inhibition of PDE3, while postoperative treatment aims at regeneration-inducing effects outlined above. The primary objective will be to compare improvement in pain or physical function at 6 months after surgery between the two arms of the trial. We hypothesise that adjuvant therapy with Ibudilast leads to a meaningful and additional improvement in either pain or function, as compared with standard routine care (decompressive surgery). Planned start date for study recruitment is September 2021, with planned end being September 2025.

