### Adaptive sample size design

The minimum clinically important difference (MCID) for the mJOA is estimated to be between 1 and 2 points.^67^ Although not exclusively validated for DCM, the MCID for VAS neck and VAS arm pain has been calculated for degenerative disease of the cervical spine with values ranging from 8 to 26 mm.^64 65^ Both VAS pain and mJOA improve more than the MCID with surgery alone,^57^ and the amount of change is linked to the pre-operative baseline.^67^ Consequently, in consensus with patients we have determined the MCID of the VAS pain score as being 1 cm and for the mJOA 1 point. This has been modelled to ensure statistical power across all baseline scenarios.

On this basis, a total sample size of 362 participants under equal randomisation will provide 85% power to detect a difference of 1 between treatment arms on the mJOA scale (assuming a SD of 2.89), using a two-sided t-test at a 2.5% significance level to adjust for multiple comparisons.^68^ The trial is also powered to detect a similar difference on the VAS neck pain scale (assuming a difference of 1 and a SD of 2.88).

A blinded interim analysis will be conducted to refine the power calculation. The aim will be to reassess the sample size in time to allow any potential extension and increase in sample size to be put into effect. Reduction in sample size will not be permitted. Any sample size increase will be based on checking the assumption regarding the SD, and will not estimate any treatment effect, hence no subsequent adjustment to future analyses is needed.

Under such a framework, the theoretical optimal time to schedule such an interim analysis would be just as the last patient is recruited under the original sample size (n=362) following which a decision could be taken to either halt or extend recruitment. However, for reasons of practicality a window for the interim analysis will be up to a period of 4 months before reaching the total sample size.

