### Statistical methods

The primary endpoint and key secondary endpoints are all measured on a continuous scale. A comparison of mean values between treatment arms, adjusting for baseline covariates, will be provided using linear regression. Estimates, standard errors, 95% CIs and p values will be provided.

For formal hypothesis testing, a closed testing approach will be used to deal with multiple endpoints.^70^ Initially either of the coprimary endpoints (mJOA or VAS neck pain) may test a null hypothesis of 0 mean difference at a two-sided 2.5% significance level,^71^ with the remaining primary endpoint tested at 5% significance level. This will enable us to determine whether the study drug is effective on pain or function independently.

Subsequently a gate-keeping approach will be used where an endpoint below the primary endpoint in the prespecified ordering is only tested if all the preceding endpoints reject the null hypothesis, using the nominal p value. If an endpoint does not reject the null, then all endpoints below it have the same conclusion, not rejecting the null, regardless of their nominal p value. The ordering is, after primary endpoints, Short Form Survey (SF-36) Physical Component Summary (PCS) and then SF-36 Mental Component Summary (MCS).

Secondary endpoints will be compared between treatment arms using approach regression techniques: linear regression for continuous endpoints, logistic regression for binary endpoints, and Cox regression for time-to-event.

The following baseline covariates, in addition to the baseline value of the endpoint, will be used to adjust all comparisons

Time to onsetSmoking status (yes/no)AgePsychiatric comorbidities (yes/no)Impaired gait (yes/no)

A detailed statistical analysis plan will be produced before the final database lock.

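### Centre is in neither the randomisation strata nor the fixed covariate list of a multicentre trial with unprotocolised surgery, a small and avoidable loss of precision in both co-primary comparisons

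*Protocol article*

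**What the plan says.** Four statements in the Protocol article bear on this point.

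- Study design and objectives: the trial is run at several centres, with Ibudilast or placebo given alongside the operation. The number of centres is not given.
- Surgery: "The surgical care of participants will therefore be at the discretion of the treating clinician and not protocolised". The section gives its reason: no approach has been shown to be better, and the choice has to suit the patient's anatomy.
- Enrolment and randomisation: allocation is 1:1 in blocks of random size, "stratifying by baseline mJOA (<12 vs ≥12), age (<60 years vs ≥60 years) and time to onset of the disease". That makes 2 × 2 × 2 = 8 strata, all defined by patient factors.
- Statistical methods: "A comparison of mean values between treatment arms, adjusting for baseline covariates, will be provided using linear regression". The covariates are then fixed: "The following baseline covariates, in addition to the baseline value of the endpoint, will be used to adjust all comparisons". The list holds time to onset, smoking, age, psychiatric comorbidity and gait impairment. It has no term for centre or for surgical approach.

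The same section says that a detailed analysis plan will be written before the final database lock.

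**The concern.** In a multicentre surgical trial, patients treated at the same centre share surgeons, operative habits and peri-operative care. If those shared features affect recovery, outcomes within a centre are correlated. A trial can deal with this in the allocation, in the model, or in both. Here the blocks are formed within patient factors, so the arms need not balance inside a centre, and the stated model has no term to absorb centre differences. Adjusting for the baseline value of the endpoint takes out part of any stable difference between centres, such as case mix. It cannot take out differences that first appear with the operation.

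What is at stake is the width of the confidence intervals for both co-primary endpoints. Which centre treated each participant is already known to the trial, so the variation could be removed at little cost.

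**Working it through.** **Inputs.** From Adaptive sample size design: difference 1, SD 2.89 for mJOA and 2.88 for VAS neck pain, two-sided 2.5% test, and "a total sample size of 362 participants under equal randomisation will provide 85% power". Assumed, because the article does not give them: ICC 0.02, 0.05 or 0.10, and 10 or 20 centres of unequal size.

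**1. The plan's own figure.** The normal approximation gives n per arm = 2 × (2.241 + 1.036)² × 2.89² / 1² ≈ 179.5, so 180 per arm and 360 in total. The exact t-test needs 181 per arm, 362 in total, with 85.1% power. The stated figure reproduces. VAS neck pain needs 360 by the t-test.

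**2. Chance imbalance of centre effects between arms.** Its mean is 0 and its SD is about 2.89 × √ICC × √(4/362):
- ICC 0.02: 0.04 points
- ICC 0.05: 0.07 points
- ICC 0.10: 0.10 points

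The target difference is 1 point, and the standard error of the comparison is 2.89 × √(2/181) ≈ 0.30. This imbalance is part of that standard error and does not come on top of it.

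**3. Ceiling on the gain.** If all centre variance were removed at no cost, the SD would fall to 2.89 × √(1 − ICC). Power at 362 (normal approximation, 85.3% without adjustment) would then be 86.1%, 87.2% or 89.0%.

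**4. Achievable gain from a centre random intercept.** Simulated with N = 362, SD 2.89, 4,000 trials per scenario, and randomisation not stratified by centre:

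| ICC | Ceiling | 10 centres, without → with centre | 20 centres, without → with centre |
|---|---|---|---|
| 0.02 | 86.1% | 85.1 → 85.8% | 85.4 → 85.7% |
| 0.05 | 87.2% | 85.1 → 86.6% | 85.1 → 85.9% |
| 0.10 | 89.0% | 85.6 → 88.3% | 85.4 → 88.1% |

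A separate run with 20,000 trials per scenario gave gains of 0.3–0.4, 0.8–1.2 and 2.6–2.8 points. A third gave 0.3–0.7, 0.9–1.4 and 2.3–2.6. Together the range is about 0.3 to 2.8 points. At ICC 0 the random intercept lost no power.

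**5. Type I error.** Without centre it was 2.2–2.7% across the simulations, and with the random intercept 2.3–2.8%, against a nominal 2.5%. The Monte Carlo error is √(0.025 × 0.975 / 4,000) ≈ 0.25 points, so neither departs from nominal.

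**6. Fixed centre effects for comparison.** These ranged from a gain of about 2 points (10 centres, ICC 0.10: 85.8 → 87.6%) to a loss of about 1 point (20 centres, ICC 0.02: 84.8 → 83.5%). This is why the random form is preferred.

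The simulations leave out the baseline covariates. The ICC that matters in practice is the one remaining after that adjustment, which may be smaller.

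**The case against.** The strongest reply is that nothing in the plan fails. The sample size reproduces. If the SD of 2.89 is a total SD, which is the natural reading for a two-arm t-test, centre variation is already inside it and the 85% target is met without a centre term. Type I error holds. Chance imbalance between centres is ordinary sampling error that the standard error already carries. All of this stands, and it limits the point to efficiency.

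The article also says that surgery alone improves both endpoints by more than the MCID. That describes an average effect and does not show that centres differ. This stands too: the ICC range is an assumption without support in the document, and a gain of more than about 1.5 points needs the top of it.

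A further reply is that the analysis plan, which is not shown, could add a centre term. That is possible. However, the covariate list is written as the one used for every comparison, so as the text stands the omission is a stated choice.

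A reader might also infer that raters at different sites score mJOA differently, or that time on drug before surgery follows local waiting lists. The article supports neither. It mentions clinician-administered and patient-reported measures only in general, does not say who scores mJOA, and expects the trial to help make assessment more uniform across centres. On timing, it says only that treatment starts within 10 weeks before surgery. The point does not need either inference.

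**Conclusion.** The point holds as a minor matter of precision. Centre is absent from both the strata and the covariates, so between-centre differences that arise after baseline remain in the residual of both co-primary comparisons. A random intercept would gain about 0.3 to 2.8 points of power at 362 participants, for an assumed ICC of 0.02 to 0.10 and 10 to 20 centres, with no loss if the ICC is zero.

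A reader might go further and infer that the treatment estimates are biased, that the error rate is inflated, or that the trial is underpowered. The documents and the calculations support none of these: randomisation protects the comparison, and both type I error and the planned power hold without centre. It would also be wrong to say that the stated analysis removes no centre differences, since adjustment for the baseline endpoint removes some.

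Leaving surgery unprotocolised is a justified pragmatic choice and is not itself a defect. Severity is low and the change is optional.

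**What to change.** In Statistical methods, and in the analysis plan before database lock, add centre as a random intercept to the linear models for mJOA, VAS neck pain and the key secondary endpoints, the SF-36 physical and mental component summaries. Keep small centres in the model as they are. Do not adjust for the surgical approach actually performed: it may be settled after randomisation and after drug has started, so it is not a baseline covariate.

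The cost is one prespecified term and a slightly more complex model, using data already held. No new data or visits are needed, and surgical discretion is untouched.

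The randomisation need not change. Full stratification by centre would give 8 × 10 to 8 × 20, that is 80 to 160 cells, for 362 participants. Switching the allocation method to minimisation during recruitment is a debatable trade-off for which no separate benefit has been shown.

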### Outcome measures and follow-up

#### Two patient-informed coprimary endpoints: pain and function

Inhibiting PDE3 and PDE4 with Ibudilast has the potential to benefit both pain and functional recovery by promoting repair mechanisms in the spinal cord as well as exerting neuroprotective effects. This provides a unique opportunity to address the most important recovery priorities identified by individuals with myelopathy. Therefore, RECEDE-Myelopathy has two outcome targets: pain and physical function.^10^ These coprimary endpoints will be assessed at 6 months after surgery, a time point when the majority of recovery will have been achieved.^57^

The study is thus powered to detect meaningful changes with regards to the coprimary endpoints independently from each other, that is, it is designed to establish whether Ibudilast has beneficial effects on function or pain alone or whether it beneficially modulates both end points.

##### Coprimary endpoint 1

The international standard, and most validated measure for assessment of function in DCM, is the mJOA score.^16 58 59^ The mJOA is a composite score of upper and lower limb muscular function, upper limb sensory function and bladder function.

##### Coprimary endpoint 2

Pain has been identified as the recovery priority of patients with DCM. The most common form is neck pain,^9^ with a neuropathic component that is responsive to neuroprotective treatments.^60 61^

While numerous tools have been developed for the measurement of pain,^62^ the Initiative on Methods, Measurements and Pain Assessment in Clinical Trials agree that pain intensity scales provide the most relevant outcome measure for demonstrating efficacy. In DCM the visual analogue scale (VAS) is the most popular example of this.^63^ Although not exclusively validated for DCM, the psychometric properties of VAS neck and VAS arm pain have been evaluated in degenerative disease of the cervical spine,^64 65^ with VAS neck pain having better repeatability.

This design will address the most important priorities of people with DCM.^10^ It leverages the mechanism of action of Ibudilast to maximise the chances of demonstrating the benefit of the studied intervention. It will increase the knowledge that can be gained through the study and demonstrate whether the proposed mechanisms of neuroprotection and regeneration can be applied to promote function and/or reduce pain. Finally, the dual end-point design will make the study more efficient than conducting two independent trials. The chosen two endpoint design will hence increase the value of the study.

### Secondary and exploratory endpoints

Clinical assessments will additionally be undertaken preoperatively, postoperatively and 3, 6 and 12 months after surgery. The disability reported in the context of DCM is wide ranging. In the absence of a consensus dataset,^51^ an issue that we are currently attending to as part of RECODE-DCM, a variety of clinician administered and patient-reported outcome measures will be used to provide a comprehensive assessment. A full list of assessments and their time points is presented in table 3.

**Table 3 T3:** Schedule of assessments

Assessments	Screening visit and initial assessments	Randomisation	Start of IMP (within 2–3 months prior to surgery)	Preoperative assessments (within 21 days prior to surgery)	Surgery	Postoperatively/ discharge (within 14 days postsurgery)	3 Months postoperatively (±21 days)	6 Months post operatively (±21 days)	12 Months post operatively (±21 days)
Informed consent	**X**								
Eligibility assessment	**X**								
Demographics	**X**								
Medical history and DCM characteristics	**X**								
Concomitant medication	**X**			**X**			**X**	**X**	**X**
Blood tests (FBC, LFT, E/U/C, TFTs)	**X**			**X**			**X**	**X**	**X**
ECG	**X**								
Urine analysis	**X**								
Pregnancy test	**X**								
Randomisation		**X**							
Neurological examination	**X**			**X**		**X**	**X**	**X**	**X**
mJOA	**X**			**X**			**X**	**X**	**X**
30 m Walk test	**X**			**X**			**X**	**X**	**X**
GRASSP-cervical myelopathy	**O**			**O**			**O**	**O**	**O**
SCIMv3	**O**			**O**				**O**	
WHO performance status				**X**					
Neck disability index	**O**			**O**		**O**	**O**	**O**	**O**
VAS pain	**X**			**X**		**X**	**X**	**X**	**X**
SF-36	**X**			**X**			**X**	**X**	**X**
EQ5D/health resource usage	**X**			**X**			**X**	**X**	**X**
Quick-DASH	**O**			**O**			**O**	**O**	**O**
Carer QoL (substudy)	**X**			**X**			**X**	**X**	**X**
Review of AEs			**X**	**X**		**X**	**X**	**X**	**X**
Dosing diary	**X**								
Dispensing of IMP			**X**			**X**	**X**		
Serum sample for PK studies	**X**			**X**	**X**		**X**	**X**	**X**
Compliance assessment				**X**		**X**	**X**	**X**	
IMP review				**X**		**X**	**X**	**X**	
Respiratory physiology and muscle function				**X**				**X**	
MRI				**X**				**X**	
Gait lab (substudy)				**X**			**O**	**X**	
Surgery details					**X**				
Surgery complications						**X**	**X**	**X**	**X**
Hospital discharge						**X**			
CSF sample					**O**				

**X: mandatory assessment; O: optional assessment**

DCM, degenerative cervical myelopathy; IMP, investigational medicinal product; mJOA, modified Japanese Orthopaedic Association; VAS, visual analogue scale.

Not all assessments will be conducted at every time point, or be mandated, to reduce participant and investigator burden. Assessment is also extended to carers of participants. Building on our preliminary finding of reduced quality of life among DCM carers,^14^ the Care Quality of Life instrument (CarerQol) will be used to evaluate this.^66^

### Adaptive sample size design

The minimum clinically important difference (MCID) for the mJOA is estimated to be between 1 and 2 points.^67^ Although not exclusively validated for DCM, the MCID for VAS neck and VAS arm pain has been calculated for degenerative disease of the cervical spine with values ranging from 8 to 26 mm.^64 65^ Both VAS pain and mJOA improve more than the MCID with surgery alone,^57^ and the amount of change is linked to the pre-operative baseline.^67^ Consequently, in consensus with patients we have determined the MCID of the VAS pain score as being 1 cm and for the mJOA 1 point. This has been modelled to ensure statistical power across all baseline scenarios.

On this basis, a total sample size of 362 participants under equal randomisation will provide 85% power to detect a difference of 1 between treatment arms on the mJOA scale (assuming a SD of 2.89), using a two-sided t-test at a 2.5% significance level to adjust for multiple comparisons.^68^ The trial is also powered to detect a similar difference on the VAS neck pain scale (assuming a difference of 1 and a SD of 2.88).

A blinded interim analysis will be conducted to refine the power calculation. The aim will be to reassess the sample size in time to allow any potential extension and increase in sample size to be put into effect. Reduction in sample size will not be permitted. Any sample size increase will be based on checking the assumption regarding the SD, and will not estimate any treatment effect, hence no subsequent adjustment to future analyses is needed.

Under such a framework, the theoretical optimal time to schedule such an interim analysis would be just as the last patient is recruited under the original sample size (n=362) following which a decision could be taken to either halt or extend recruitment. However, for reasons of practicality a window for the interim analysis will be up to a period of 4 months before reaching the total sample size.

The SD and correlation of both endpoints will be reassessed using data pooled across the arms. The three possible statistically significant conclusions of the formal hypothesis testing (VAS; mJOA; both) will be provided with revised target sample sizes needed to achieve 85% power under the same MCID values, but with revised estimates for the SD values and correlation. A recommended revised sample size will be the smallest of the three new target sample sizes or the original sample size if this is larger; hence the recommended sample size will never be a reduction from the original.

The next step of the interim analysis will be to calculate the conditional power of the three possible positive outcomes based on, the estimated unblinded treatment effects from the current data, plus, the distribution of future data from the revised sample size under the corresponding combinations of true treatment effects (MCID or zero), and SD and correlation estimates from the first step. If all three conditional power values are <30% then the recommendation would be to halt the study.

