Of note, typical daily dosing in these trials ranged from 60 to 100 mg, which is greater than the currently licensed dosing of 10–20 mg per day for routine clinical practice. While trials confirmed overall tolerability and safety for use of Ibudilast in these doses in humans, findings do indicate a dose-dependent relationship for gastrointestinal side effects, such as nausea, and headaches and, in a minority of cases, this led to discontinuation of therapy by participants.

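### The stated 85% power belongs to 362 participants analysed at 6 months, but 362 is also the number to be recruited, so under the stated t-test it leaves no room for missing data

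*Protocol article*

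**What the plan says.** All from the protocol article.

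- *Adaptive sample size design* states that "a total sample size of 362 participants under equal randomisation will provide 85% power to detect a difference of 1 between treatment arms". The inputs it gives for mJOA are an SD of 2.89 and a t-test, two-sided, with alpha set to 2.5% because there are two coprimary endpoints. It makes the same claim for VAS neck pain, with an equal difference and an SD of 2.88.
- The same section places the ideal moment for the interim analysis "just as the last patient is recruited under the original sample size (n=362"), so 362 is also the original recruitment total. *Enrolment and randomisation* says participants are "enrolled and randomised at 1:1 to one of the two treatment arms".
- On re-estimation: "Any sample size increase will be based on checking the assumption regarding the SD". The revised targets use the same differences with updated SDs and correlation. The recommendation is the smallest of three targets, and never below 362.
- *Outcome measures and follow-up* claims power for each coprimary endpoint independently of the other, with both assessed 6 months after surgery.
- *Statistical methods* plans linear regression adjusted for the baseline value and five further covariates. One coprimary may be tested at 2.5% and the remaining one at 5%.

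**The concern.** A number needed for analysis and a number to be recruited coincide only if nobody's endpoint is missing. Treatment starts up to 10 weeks before surgery and the endpoint falls 6 months after it, so up to about 8 months separate the two. *Ethical approval and dissemination* allows withdrawal at any time. Some missing 6-month data should therefore be expected.

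This is more than a detail left to the full protocol. The article gives both uses of 362 together with all the inputs, and at those inputs the figure cannot contain an allowance. A reader would take 85% as the power of the trial as recruited. The interim review, which looks like the natural safeguard, is built to respond to the SDs and correlation and to nothing else.

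**Working it through.** **Inputs** (*Adaptive sample size design*): difference δ = 1; SD σ = 2.89 (mJOA) and 2.88 (VAS); two-sided α = 0.025; t-test; equal arms; 362 in total, or 181 per arm. Loss rates of 5% to 20% are assumptions, because the article gives none.

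**Formula.** With n per arm, the test statistic is noncentral t with 2n − 2 degrees of freedom and noncentrality δ / (σ√(2/n)). Power is the probability that it exceeds the two-sided 2.5% critical value in absolute size.

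**Step 1: reproduce the plan's figure.**
- mJOA, n = 181: noncentrality 1 / (2.89 × √(2/181)) = 3.292, critical value 2.251, power 85.06%.
- mJOA, n = 180: power 84.84%. The minimum is 181 per arm, or 362, with no slack.
- VAS, n = 181: power 85.3%. At n = 180 it is 85.1% and at n = 179 it is 84.9%. The minimum is 360, so there are two participants of slack.

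**Step 2: recruit 362 and lose a share d of the 6-month data.**

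| Loss (assumed) | Analysed | mJOA power | VAS power |
|---|---|---|---|
| 0% | 362 | 85.1% | 85.3% |
| 5% | 344 | 83.0% | 83.3% |
| 10% | 326 | 80.8% | 81.1% |
| 15% | 308 | 78.3% | 78.6% |
| 20% | 290 | 75.5% | 75.9% |

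**Step 3: does the interim rule respond?** Its inputs are the fixed differences, the re-estimated SDs and the correlation. If the SDs prove as assumed, VAS alone needs 360, so the smallest target is no more than 360 and the floor returns 362, whatever the retention. If an SD proves larger, any increase pays for the SD and not for missing endpoints.

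**Step 4: what baseline adjustment could recover.** If the stated SDs are unadjusted, adjusting for a baseline value with correlation ρ to the outcome reduces the SD to σ√(1 − ρ²). This offsets a loss d when (1 − d) / (1 − ρ²) = 1, that is, when ρ = √d:
- 10% loss: ρ = √0.10 ≈ 0.32
- 20% loss: ρ = √0.20 ≈ 0.45

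At an assumed ρ of 0.4 the SD becomes 2.89 × √0.84 = 2.65, and mJOA power is about 87.6% at 10% loss and 83.1% at 20%. At ρ = 0.3 it is 84.6% at 10% loss.

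**Step 5: what the second test at 5% could recover.** This was simulated with a normal approximation, which runs about 0.3 points above the t-test. Both effects are taken as real and the endpoint correlation is assumed to lie between 0 and 0.5. mJOA power is then about 89% to 90% with complete data, 85.5% to 86.6% at 10% loss and 80.8% to 81.9% at 20% loss. If VAS has no effect, this gain all but disappears and the table in step 2 applies.

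**The case against.** The strongest reply is that nothing is miscalculated and that the t-test is not the planned analysis. Both points are true. The arithmetic is exact, and the regression adjusts for baseline, which the article itself says is linked to the amount of change. A moderate correlation would cover ordinary losses. The table in step 2 is thus the unadjusted end of a range. What remains is that the article states its power for a t-test, does not say whether its SDs are adjusted, gives no baseline-outcome correlation and does not say that adjustment is meant to absorb losses.

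A second reply is that the trial succeeds on either endpoint. If both effects are real, the chance of at least one success at 10% loss is about 92% to 97% (endpoint correlation 0.5 to 0). That stands, and it confines the shortfall mainly to the case where one endpoint responds. The article claims power for that case explicitly.

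Three stronger readings are tempting, and the documents do not support them:
- *Any loss takes both endpoints below 85%.* This is true of mJOA only. VAS can lose two participants, although in practice that is immaterial.
- *Stopping the drug lowers power further.* The article says of gastrointestinal side effects and headaches in other trials that "in a minority of cases, this led to discontinuation of therapy by participants". Stopping treatment is not a missing 6-month assessment. The article gives no expected rate here, no size for the lost effect, and no statement on whether the 1-point difference already allows for it. No power figure can be drawn from it.
- *The trial is underpowered and must enrol more.* Given steps 4 and 5, that cannot be shown from the article.

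**Conclusion.** The point holds as a misstatement of what 85% refers to. At the stated inputs, 362 is the complete-data number for mJOA and within two participants of it for VAS, while the article also treats it as the number recruited. Under the stated t-test, power for one endpoint on its own falls by about 2 points at 5% loss, 4 at 10%, 7 at 15% and 9 to 10 at 20%. The re-estimation does not correct this.

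The sizes rest on assumed loss rates, on the stated SDs, and on analysis without covariate gain. If the SDs are unadjusted and baseline predicts outcome moderately well, the shortfall may disappear. It is a moderate point that should be corrected in the text, and it does not threaten the validity of the trial.

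**What to change.** 1. In the sample size text, state that 362 is the number of participants with 6-month mJOA and VAS data.
2. Either give the power for each endpoint over a range of losses, such as 5% to 20%, or state the baseline-outcome correlation relied on to absorb them and whether 2.89 and 2.88 are unadjusted SDs.
3. At the blinded interim, report the pooled retention rate and the power at the expected analysable number beside the SD-based targets. This needs no treatment-effect estimate.

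The cost is a few sentences, one extra line in the interim report and possibly a less favourable stated power. Whether to recruit more is a separate decision for the sponsor and not part of this fix. It would not be free: keeping 362 analysable at 10% loss means 362 / 0.90 = 402.2, so 403 recruited, and at 20% loss 362 / 0.80 = 452.5, so 453.
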